### **1.5. The RTS,S/AS01B candidate malaria vaccine; preliminary clinical safety, efficacy and immunogenicity data**

Recent preliminary results of a challenge study conducted in healthy malaria-naïve adults have been encouraging (Malaria-027 [GSK data on file]), indicating that RTS,S/AS01B may be more efficacious than RTS,S/AS02A. In this double-blind, randomized phase I/IIa human challenge study, the safety, reactogenicity, immunogenicity and preliminary efficacy after early sporozoite challenge and rechallenge, of RTS,S/AS01B and RTS,S/AS02A were assessed. Two sequential cohorts of approximately 52 subjects each were enrolled; each cohort was evenly divided into 2 groups receiving either the RTS,S/AS01B or RTS,S/AS02A vaccine (up to 48 infectivity controls for challenge and re-challenge phases were additionally enrolled). Subjects were vaccinated at 0, 1, 2 months followed by a challenge 14-30 days after Dose 3. Protected individuals were invited to be rechallenged approximately 6 months after Dose 3 to evaluate persistence of efficacy. To date, preliminary results for Cohort 1 are available.

Following primary challenge, the point efficacy of VE was significantly greater in both vaccine groups compared to infectivity control. Although not statistically significant, VE was higher in the RTS,S/AS01B group compared to RTS,S/AS02A (58.8% [95% CI: 32.1, 81.6] vs 37.5% [95% CI: 11.8, 59.4],  $p=0.2085$ ). In non-protected subjects, the mean time to infection (pre-patent period; PPP) following challenge was similar in both vaccine groups and longer than in the infectivity control.

Following re-challenge, 2/5 subjects (40.0%) in the RTS,S/AS01B group and 4/5 subjects (80.0%) in the RTS,S/AS02A group were infected; all infectivity control subjects became infected. VE was significantly greater in the RTS,S/AS01B group compared to infectivity control ( $p=0.061$ ) and greater compared to RTS,S/AS02A (60.0% [95% CI: 3.2, 95.1] vs 20.0% [95% CI: -60.2, 71.6], respectively). The PPP in non-protected subjects was longer in the RTS,S/AS01B group compared RTS,S/AS02A; PPP was longer in both vaccine groups compared to control.

The reactogenicity and safety profile of RTS,S/AS01B was comparable to RTS,S/AS02A. Both vaccines were shown to be safe, immunogenic and efficacious; two SAEs were reported (tendon rupture, cerebral infarction), both in the RTS,S/AS01B group, neither of which was considered to be related to study vaccine; anti-CS antibody

responses were greater in recipients of RTS,S/AS01B than of RTS,S/AS02A; anti-CS CD4+ T-cell responses were stronger in the RTS,S/AS01B group compared to RTS,S/AS02A; there was a trend towards improved efficacy with RTS,S/AS01B compared to RTS,S/AS02A.

## **1.6. Rationale for the study design**

RTS,S/AS01 has been developed as a potential improvement to the RTS,S/AS02 vaccines. Preliminary results from the Malaria-027 trial indicate that the RTS,S/AS01B formulation may be more efficacious than RTS,S/AS02A while retaining its acceptable reactogenicity profile (refer to Section 1.5). RTS,S/AS01E is a pediatric formulation of RTS,S/AS01B, designed to be compatible with the requirement that all vaccines administered under the EPI of WHO have a dose volume of 0.5 mL.

This trial is designed to assess the safety of RTS,S/AS01E and demonstrate non-inferiority of the anti-CS immune response to RTS,S/AS02D in children aged 18 months to 4 years. This approach is implemented to ensure safety and immunogenicity of the new formulation before proceeding to trials in younger children and infants.

There are two reasons why the RTS,S/AS01E candidate malaria and hepatitis B vaccine is being developed for delivery through the infant Expanded Program on Immunization (EPI) of the World Health Organization (WHO). Firstly, the vaccine is being developed to prevent severe malaria disease which occurs from about 4 months of age coinciding with the time that maternally-acquired immunity wanes [Snow 1990; Snow 1994]. Secondly the EPI has been highly successful at increasing the coverage of basic vaccines across the developing world. With the goal of integration into the EPI infant regimen, a 0, 1, 2 month schedule will be evaluated in children and the final dose volume is adjusted to 0.5 mL to be compatible with the standard syringes used by EPI.

### **1.6.1. Rationale for CMI and B-cell memory testing**

Neutralizing-antibody and CMI responses are thought to be essential immune effector mechanisms for protecting people vaccinated with RTS,S/AS02 and RTS,S/AS01. It is hypothesized that these responses act to limit hepatocyte invasion, destroy infected hepatocytes and/or limit intracellular parasite development.

RTS,S/AS02A has been shown to be a powerful inducer of antigen-specific humoral and CMI responses in preclinical and clinical studies [Malaria Investigator's Brochure 2005 GSK data on file]. Recent preliminary results of a challenge study conducted in healthy malaria-naïve adults (Malaria-027 [GSK data on file]) shows that RTS,S/AS01B induces more potent CMI responses characterized predominantly by CD4+ type 1 responses and similar antibody levels as compared to RTS,S/AS02A. This may be associated with increased vaccine efficacy on the part of RTS,S/AS01B; immunological monitoring performed during this trial revealed an association between protection against *P. falciparum* and CS-specific humoral and cellular response ([name], WRAIR, personal communication, November 2005; publication in preparation).

CMI and B-cell memory immune responses induced by a vaccine antigen formulated in AS01 adjuvant have never been measured in children. We will compare CMI responses in children vaccinated with RTS,S/AS01E and RTS,S/AS02D, as this may reflect differences in vaccine efficacy. Responses will be measured on cells taken prior to vaccination, one month post Dose 2, one month post Dose 3, and 12 months post Dose 3. Antigen-specific B-cell memory immune response will also be characterized, as this may provide useful data regarding the respective ability of both adjuvants to induce long-term humoral immunity.

In order to limit the blood volumes collected from children, CMI and B-cell memory immune responses will not be determined in the same children. Half of the children will have CMI assessed, and the other half will have B-cell memory immune response characterized. Details of the assay methodology can be found in Appendix F. Attribution will be determined by a randomization list and balanced by vaccine assignment.

## **2. OBJECTIVES**

### **2.1. Coprimary objectives**

- For RTS,S/AS01E when administered as 3 doses intramuscularly on a 0, 1, 2-month schedule to children aged 18 months to 4 years living in a malaria-endemic area:
  - to assess safety until one month post Dose 3
  - to demonstrate non-inferiority to RTS,S/AS02D in terms of anti-CS antibody response one month post Dose 3.

Refer to Section 10.1 for definition of the coprimary endpoints.

### **2.2. Secondary objectives**

- For RTS,S/AS01E when administered as 3 doses intramuscularly on a 0, 1, 2-month schedule to children aged 18 months to 4 years living in a malaria-endemic area:
  - to assess reactogenicity until one month post Dose 3
  - to demonstrate non-inferiority to RTS,S/AS02D in terms of anti-HBs antibody response one month post Dose 3
  - to describe seroprotection against hepatitis B up to one month post Dose 3
  - to describe the anti-CS response up to one month post Dose 3.

Refer to Section 10.2 for definitions of secondary endpoints.

### 2.3. Tertiary objectives

- To assess, for RTS,S/AS01E when administered as 3 doses intramuscularly on a 0, 1, 2-month schedule to children aged 18 months to 4 years living in a malaria-endemic area:
  - safety between 1 month post Dose 3 until 12 months post Dose 3.
  - humoral immune response to CS antigen at 12 months post Dose 3
  - humoral immune response to HBs antigen at 12 months post Dose 3.

Refer to Section 10.3 for definitions of tertiary endpoints.

### 2.4. Exploratory Objectives

- For RTS,S/AS01E and RTS,S/AS02D when administered as 3 doses intramuscularly on a 0, 1, 2-month schedule to children aged 18 months to 4 years living in a malaria-endemic area:
  - to evaluate T-cell-mediated immune response (CMI) to CS antigen up to 12 months post Dose 3
  - to evaluate B-cell memory immune response to CS antigen up to 12 months post Dose 3.

Refer to Section 10.4 for definitions of exploratory endpoints.

## 3. STUDY DESIGN OVERVIEW

[figure not shown]

KEY: BS; Blood Sample. Vacc; Vaccination

- Experimental design: Phase II, single center, double-blind (observer blind, participant blind), randomized (1:1 ratio) trial with two groups in one study site.
- Healthy male and female children aged 18 months to 4 years of age will be screened; those determined to be eligible, based on the inclusion and exclusion criteria, will be enrolled in the study.

- Route of administration: all vaccines will be administered by the intramuscular route to the left deltoid.
- Each child will be observed for at least 60 minutes after vaccination to evaluate and treat any acute adverse events (AEs).
- This study will not capture cases of malaria for the analysis of efficacy. All cases of malaria presenting during the unsolicited period will be captured as unsolicited events. Cases at anytime during the study that meet the criteria for a SAE will be reported as SAEs.
- The access of the study population to HIV voluntary counseling and testing and HIV antiretroviral therapy according to national recommendations will be ensured, in collaboration with the government services.
- An insecticide impregnated bednet will be offered to all parent(s)/guardian(s) who present their child for screening.
- Blood for safety monitoring of hematology, renal and hepatic function will be measured at screening, one week post Dose 1, one month post Dose 3 and 12 months post Dose 3.
- Anti-CS antibody titers will be determined at screening, one month post Dose 2, one month post Dose 3 and 12 months post Dose 3.
- Anti-HBs antibody titers will be determined at screening, one month post Dose 2, one month post Dose 3 and 12 months post Dose 3.
- CMI and B-cell memory immune responses will be determined at screening, one month post Dose 2, one month post Dose 3 and 12 months post Dose 3.
- Timing of final analysis: 1 month post Dose 3. An annex safety analysis will be performed at the end of the study, one year post Dose 3.
- Data collection: conventional Case Report Form (CRF).

## **4. STUDY COHORT**

### **4.1. The Albert Schweitzer Hospital Medical Research Unit**

This study will be conducted at the Medical Research Unit (MRU) of the Albert Schweitzer Hospital (HAS – Hôpital Albert Schweitzer) in Lambaréné, Gabon. The HAS was founded in 1913. It is run by the International Foundation of the HAS in collaboration with the Ministry of Health of Gabon.

The MRU of the HAS was established in 1981. The scientific focus is on malaria research, and main areas of interest are parasite biology, pathophysiology, pathogen-host interaction, host immune response, clinical aspects and chemotherapy of malaria. Other areas of research comprise schistosomiasis, filariases and mechanisms of allergy development.

There are three research groups within the MRU: Clinical Trials, Molecular Epidemiology and Immunology. Currently the groups are staffed by approximately 30

temporary and permanent staff affiliated to an academic institution. Among these are several post-doctoral scientists as well as PhD and MD students.

The Clinical Trials group has a staff of four medical doctors, all of whom have had additional training in specific aspects of clinical trials (basic and advanced courses on clinical research, publication workshops, biostatistics and epidemiology). Technical staff comprises three technicians, who are responsible for routine laboratory diagnostics of pediatric out-patients and study subjects.

Annually, around ten students do research for their thesis in medicine at the unit. Such students come from both the University of Libreville and European universities.

The laboratory of the unit is well-equipped with a photometer, a cytometer, sterile workbenches and -80°C freezers. Implementation of a quality-control system is currently being planned. Hematological, biochemical and serological testing can all be carried out at HAS.

The unit has good information technology capability. Internet connectivity is provided via a satellite link with the MIMCOM network (Multilateral Initiative on Malaria Communications). An information technology manager is responsible for database management and the computer network. Several unit staff have a background in epidemiology and basic statistical analysis. When necessary, more sophisticated analytical support has been provided by the Department of Parasitology or the Department of Biometry, University of Tübingen, Germany.

The MRU receives no annual core budget, financing itself entirely through research projects and grant money. In the past the MRU has received funding from the European Union, the Medical Faculty of the University of Tübingen, the German Ministry of Research, the US National Institute of Health, WHO/TDR (Special Programme for Research and Training in Tropical Diseases), and the pharmaceutical industry. Currently a large proportion of the funding comes from the German MIM initiative as well as some other German research programmes.

The MRU has conducted many clinical trials to ICH/GCP standard. The internal review board, the Ethics Committee of the International Foundation of the HAS is registered with the US Department of Health and Human Services.

## **4.2. Geography and study population**

The HAS is situated in Lambaréné, a town of approximately 20 000 inhabitants. Lambaréné is located in the Moyen Ogooué province of Gabon near the equator in the central African rain forest. There is little variation in temperature and humidity throughout the year, however there is substantially less rainfall in July and August.

The population consists of several Bantu groups, mainly belonging to the Fang, Eshira and Myéné group. Inter-marriage between members of different tribes is common. Local languages are mainly spoken on the family level but have little importance in official life, where French is used. According to United Nations Children's Fund, the adult literacy

rate in 2000 was 71% (for males 80%, for females 62%). Timber and palm oil industries exist in town. Fishery and hunting is performed on a smaller scale but is of major importance. People in the study area live in clusters of houses close to roads with easy access to taxis and with telecommunications services.

### **4.3. Malaria epidemiology and control in the study area**

Malaria transmission in the study area is intense and there is little seasonal variability in transmission rates or parasite prevalence [Wildling 1995; Sylla 2001]. *Plasmodium falciparum* is the predominant species and responsible for 95% of all infections. The main vectors are *Anopheles gambiae* and *An. moucheti*. The entomological inoculation rate lies around 50 infective bites per person per year [Sylla 2000].

The level of chloroquine resistance is high, reaching 100% both in vitro and in vivo [Borrmann 2002]. Resistance of local parasite strains to sulfadoxine/pyrimethamine is moderate and rising steadily. A recent study in Lambaréné found a treatment failure of 21% in children on Day 14 [Allouche 2004]. The policy of the government of Gabon is to treat all children with malaria with Artemisinin-based Combination Therapy (ACT).

On average, children aged 2 to 12 years experience about 1.5 malarial attacks per year, with large variability among individuals [[name] 1999]. Anemia is common: around 70% of children tested at HAS MRU have Hb < 9g/dL; about 17% of children have Hb < 5g/dL [[name] unpublished].

There is no widely implemented national or local bednet programme. Although part of the population sleep under bednets, these are rarely impregnated, installed properly or well-maintained.

### **4.4. Healthcare in the study area**

Primary healthcare in the study area is available through dispensaries throughout Lambaréné. These offer vaccination services, mother and child healthcare and midwifery services (including delivery). In addition to the HAS, there is a government-run district hospital in the center of Lambaréné offering district level care. No consultation fees are levied at the District General Hospital, but patients are charged for each procedure carried out.

HAS is located on the outskirts of Lambaréné town but well integrated into the care of the community. There are approximately 200 staff at the HAS, headed by 8 physicians. In total, approximately 200 beds are available to departments of internal medicine, surgery, pediatrics and obstetrics. In addition there is a dental clinic, a community health service where mother and child vaccinations are administered, and the MRU. The pediatric clinical service of HAS is led by two specialist pediatricians. The pediatric ward can offer a number of diagnostic and clinical services that are unavailable elsewhere in Lambaréné. Medical care is available at HAS 24 hours a day.

The pediatric ward has the ability to provide district level clinical care. Emergency services are also available. There are basic blood bank services; donations are screened

for infection with HIV, hepatitis B virus, hepatitis C virus, loa loa and syphilis. X-ray and ultrasound facilities are available. Cases requiring more extreme intensive care, as well as cases of renal insufficiency, endocrine abnormalities or suspected malignancies can be transferred by ambulance the Centre Hospitalier de Libreville, a 3 to 4 hours drive. A consultation fee is levied by HAS, but this fee is inclusive of all charges for procedures.

#### **4.4.1. HIV services**

The HIV seroprevalence is an estimated 4% [Debat Zoguereh 2004]. At HAS, HIV testing is performed using Determine® (Abbott Laboratories, Illinois, USA). A positive or inconclusive test is validated using ImmunoComb® (Organics, Yavne, Israel). The HAS is one of the centers of the national programme for HAART (highly active antiretroviral therapy) distribution. Voluntary counseling and CD4 count testing are available. Treatment for the patient is provided free of charge.

#### **4.5. Number of subjects**

Children will be recruited by non-coercive methods according to existing policies of the study site (see Appendix C).

The necessary number of children will be screened in order to enroll approximately 180 eligible subjects, 90 to each group. See Section 10.5 for a detailed description of the criteria used in the estimation of sample size.

#### **4.6. Inclusion criteria for enrolment**

All subjects must satisfy the following criteria at study entry:

- A male or female child between 18 months and 4 years of age (up to but not including 5th birthday) at the time of first vaccination.
- Written or oral, signed or thumb-printed and witnessed informed consent obtained from the parent(s)/guardian(s) of the child.
- Subjects who the investigator believes that their parents/guardians can and will comply with the requirements of the protocol (e.g. return for follow-up visits) should be enrolled in the study.

#### **4.7. Exclusion criteria for enrolment**

The following criteria should be checked at the time of study entry. If any apply, the subject must not be included in the study:

- Acute disease at the time of enrolment (acute disease is defined as the presence of a moderate or severe illness with or without fever). All vaccines can be administered to persons with a minor illness, such as diarrhea or mild upper respiratory infection without fever, i.e. axillary temperature < 37.5°C.

- Serious acute or chronic illness determined by clinical or physical examination and laboratory screening tests including, but not limited to:
  - Any confirmed or suspected immunosuppressive or immunodeficient condition, based on medical history and physical examination (no laboratory testing required)
  - A family history of congenital or hereditary immunodeficiency
  - History of splenectomy
  - Major congenital defects
  - History of any neurologic disorders or seizures
  - Moderate malnutrition at screening defined as weight for age Z-score less than -2.
- Laboratory screening tests out of range, specifically:
  - refer to Table 10
- Planned administration/administration of a vaccine not foreseen by the study protocol within 30 days of the first dose of vaccine(s) with the exception of tetanus toxoid.
- Use of any investigational or non-registered drug or vaccine within 30 days preceding the first dose of study vaccine, or planned use during the study period.
- Administration of immunoglobulins, blood transfusions or other blood products within the three months preceding the first dose of study vaccine or planned administration during the study period.
- Chronic administration (defined as more than 14 days) of immunosuppressants or other immune-modifying drugs within six months prior to the first vaccine dose (for corticosteroids, this will mean prednisone, or equivalent,  $\geq 0.5$  mg/kg/day. Inhaled and topical steroids are allowed).
- Previous participation in any other malaria vaccine trial.
- Simultaneous participation in any other clinical trial.
- Same sex twin.
- History of allergic reactions (significant IgE-mediated events) or anaphylaxis to previous immunizations.
- History of allergic disease or reactions likely to be exacerbated by any component of the vaccine.
- Any other findings that the investigator feels would increase the risk of having an adverse outcome from participation in the trial.

#### **4.8. Elimination criteria during the study**

The following criteria should be checked at each visit subsequent to the first visit. If any become applicable during the study, it will not require withdrawal of the subject from the

study but may determine a subject's evaluability in the according-to-protocol (ATP) analysis.

- Administration of a vaccine (except tetanus toxoid) not foreseen by the study protocol during the period starting from 30 days before Dose 1 and ending 30 days after Dose 3.
- Use of any investigational or non-registered product (drug or vaccine) other than the study vaccines during the study period.
- Administration of immunoglobulins and/or any blood products during the study period.
- Chronic administration (defined as more than 14 days) of immunosuppressants or other immune-modifying drugs during the study period (for corticosteroids, this will mean prednisone, or equivalent,  $\geq 0.5$  mg/kg/day. Inhaled and topical steroids are allowed).

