| STUDY CONCLUSION                                                     |                |                    |                |                |                |                |                |                |                |                    |                |

#: Field Worker visit code numbers not necessarily sequential. ● is used to indicate a study procedure that requires documentation in the individual CRF and ○ is used to indicate a study procedure that does not require documentation in the individual CRF.

a: includes analysis of hemoglobin, total white cell count and platelets

b: SAEs related to study procedures will be collected

c: all medications required by protocol to be recorded at these visits

d: record administration of immunosuppressants or other immune-modifying drugs during this period (for corticosteroids this means prednisone or equivalent,  $\geq 0.5$  mg/kg/day. Inhaled or topical steroids are allowed and should not be recorded. ALSO all immunoglobulins and blood products should be recorded during this period.

It is the investigator's responsibility to ensure that the intervals between visits/contacts are strictly followed. These intervals determine each subject's evaluability in the according to protocol analyses (see Sections 4.6 to 4.9 and Section 10.6 for details of criteria for evaluability and cohorts to be analyzed). The intervals are tabulated in Table 4.

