## **6.9. Concomitant medication/treatment**

At each study visit/contact, the investigator should question the enrolled subject's parent(s)/guardian(s) about any medication(s) taken.

All antipyretic, analgesic and antibiotic drugs, administered at ANY time during the period starting with administration of each dose and ending 30 days after each dose of vaccine are to be recorded with generic name of the medication (trade names are allowed for combination drugs, i.e., multi-component drugs), medical indication, total daily dose, route of administration, start and end dates of treatment.

Any treatments and/or medications which are listed as elimination criteria in Section 4.8, e.g., any immunoglobulins, other blood products and any immune modifying drugs administered within three months preceding the first dose or at any time during the study period are to be recorded with generic name of the medication (trade names are allowed for combination drugs only), medical indication, total daily dose, route of administration, start and end dates of treatment. Refer to Sections 4.7 to 4.9. The time periods between which each type of concomitant medication/treatment should be recorded is summarized in Table 8.

**Table 8            Summary of time periods between which different classes of concomitant medication/treatment/vaccination must be recorded**

|                                                |                                                                                                                              |
|------------------------------------------------|------------------------------------------------------------------------------------------------------------------------------|
| 3 months prior to Dose 1 → Dose 1       | All treatments listed as elimination criteria in Section 4.8*                                                                |
| Screening → 30 Days post Dose 3         | All antipyretic, analgesic, antibiotic and any treatments listed as elimination criteria in Section 4.8*
All vaccinations |
| 31 Days post Dose 3 → Final Study Visit | All treatments listed as elimination criteria in Section 4.8*                                                                |

\* e.g. any immunoglobulins, other blood products and any immune modifying drugs

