Any vaccine not foreseen in the study protocol administered in the period beginning 30 days preceding each dose and ending 30 days after each dose is to be recorded with trade name, route of administration and date(s) of administration. Refer to Sections 4.7 to 4.9.

Any concomitant medication administered prophylactically in anticipation of reaction to the vaccination must be recorded in the CRF with generic name of the medication (trade names are allowed for combination drugs only), total daily dose, route of administration, start and end dates of treatment and coded as 'Prophylactic'.

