### **10.3. Tertiary endpoints**

#### **10.3.1. Immunogenicity**

*At Study Month 14:*

- Anti-HBs antibody titers determined 12 months post Dose 3.
- Anti-CS antibody titers determined at 12 months post Dose 3.

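### Hepatitis B vaccination after about Day 90 is neither required to be recorded nor an elimination criterion, so the Month 14 anti-HBs GMT may include boosted children whom the required data do not show

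*Protocol*

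**What the plan says.** **Elimination.** Protocol Section 4.8 counts a vaccine outside the protocol (tetanus toxoid excepted) as an elimination criterion "during the period starting from 30 days before Dose 1 and ending 30 days after Dose 3". Its other criteria run for the whole study. One is "Use of any investigational or non-registered product (drug or vaccine) other than the study vaccines during the study period"; the others concern immunoglobulin or blood-product use and chronic immunosuppressive or immune-modifying treatment.

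**Recording.** Section 6.9 says that a vaccine outside the protocol given "in the period beginning 30 days preceding each dose and ending 30 days after each dose is to be recorded". Table 8 lists "All vaccinations" in its row from screening to 30 days post Dose 3. The next row, which runs to the final visit, has no such entry and refers only to treatments that Section 4.8 lists as elimination criteria. Its examples are immunoglobulins, blood products and immune-modifying drugs. For Months 4 to 14, Table 3 footnote d asks staff to "record administration of immunosuppressants or other immune-modifying drugs during this period", and adds immunoglobulins and blood products. It names no vaccine. HBV immunization status is recorded at screening only (Table 3; Clinic Visit 1 in Section 5.11).

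**Endpoint.** Section 10.3.1 lists "Anti-HBs antibody titers determined 12 months post Dose 3" as a tertiary endpoint. Section 10.9.2 bases the Month 14 immunogenicity analysis primarily on the ATP cohort. Section 10.9.2.1 reports the seroprotection rate, the GMT with 95% CI, and reverse cumulative curves.

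**The concern.** The exposure that acts most directly on the Month 14 anti-HBs titer is a hepatitis B vaccine. Section 1.3 says that the HBsAg in RTS,S comes from a gene identical to the one used for the sponsor's licensed hepatitis B vaccine. A later dose of such a vaccine would therefore add to the same antibody that the endpoint measures, and the titer does not reveal its source. Section 4.4 shows that child vaccination is available locally, both at dispensaries and at the trial hospital.

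The protocol follows immunoglobulins and blood products to Month 14 but not this exposure. If some children are boosted, the reported Month 14 GMT mixes the response left from the study vaccine with the response to another product. An analysis plan can say how to handle boosted children, but it cannot supply an exposure that the CRF was never required to hold.

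**Working it through.** The plan gives no figure on this point, so the check compares time windows and adds an illustration.

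**1. The windows.** Dose 3 falls on Day 60 (Section 5.11), and 60 + 30 = Day 90. The dosing intervals in Table 4 (21 to 35 days each) put Dose 3 between Day 42 and Day 70, so the window closes between Day 72 and Day 100. From about Month 3 to the Month 14 sample, 14 − 3 = 11 months are uncovered.

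| Provision | Covers a registered hepatitis B vaccine at, say, Month 8? |
|---|---|
| 4.8, vaccine criterion | No: it ended 30 days after Dose 3 |
| 4.8, whole-study criteria | No: they cover experimental or unlicensed products, immunoglobulins and blood products, and immunosuppressants |
| 6.9, vaccine recording | No: it ended 30 days after Dose 3 |
| Table 8, last row | No: vaccinations are not listed |
| Table 3, footnote d | No: vaccines are not named |
| HBV immunization status | No: screening only |

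Table 8's last row could be read as reaching vaccines through its reference to Section 4.8. That reading fails: the vaccine criterion has expired by then, the row's examples name no vaccine, and both footnote d and the text of Section 6.9 take the narrower view. The check of elimination criteria at Visit 7 has the same limit.

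**2. Possible effect on the GMT (assumed inputs).** Let p be the fraction of a group boosted and k the average (geometric) fold-rise still present at Month 14. The mean log10 titer rises by p × log10(k), so the GMT is multiplied by k^p.

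- p = 2%, k = 10: 10^0.02 = 1.05
- p = 5%, k = 30: 30^0.05 = 1.19
- Wider grid, k from 5 to 50: 1.03 to 1.08 at p = 2%; 1.08 to 1.22 at p = 5%; 1.17 to 1.48 at p = 10%

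The protocol gives neither p nor k.

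**3. Scale against precision.** Section 10.5 gives a log SD of 0.9, for anti-CS only. It reproduces the planned 75 per group on the log10 scale: 2 × 0.9² × (1.960 + 1.282)² / (log10 3)² = 74.8, rounded up to 75, with power of 90.1%. A natural-log SD would give 15. If anti-HBs had the same SD (an assumption), the half-width of the 95% CI of one group's GMT would be 1.96 × 0.9 / √75 = 0.204 log10, a factor of 1.6. Shifts of 1.05 to 1.19 lie inside that. They are a bias, however, and would not shrink with more children.

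**The case against.** The strongest reply accepts the gap in the text and disputes its consequence. Most of that reply stands.

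- **No test is affected.** The endpoint is tertiary and descriptive. The anti-HBs non-inferiority comparison is made one month post Dose 3 (Section 10.8.2), a time that the existing vaccine window covers. A reader might infer that boosting hides a difference between the vaccines. The protocol plans no Month 14 between-group test or margin for it to hide from.
- **No arm is favoured.** A reader might infer that RTS,S/AS01E gains an advantage. Both groups receive RTS,S, allocation is randomized and blinded, and nothing in the protocol suggests that later hepatitis B vaccination would differ by group.
- **Seroprotection is probably near its ceiling.** Section 1.4 reports at least 97% seroprotected 18 months after Dose 3 of RTS,S/AS02A in Mozambican children. If this trial is similar, the rate has little room to rise. The GMT has no such ceiling.
- **Some cases might be traced.** A reader might infer that boosted children could never be found. Parents are asked about medication at each contact (Section 6.9), and outpatient attendances at the trial hospital are recorded comprehensively (Section 5.7.1). Site records could reveal some vaccinations, but nothing requires them to be sought or entered, and a dose given elsewhere could be missed.
- **The Report and Analysis Plan could define the Month 14 cohort.** It could, but only if the vaccination data exist.

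The frequency may also be negligible. The documents cannot settle that either way.

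**Conclusion.** The gap is real but modest in consequence. A registered hepatitis B-containing vaccine given between about Day 91 and Month 14 is neither required to be recorded nor grounds for elimination. Boosted children therefore cannot be identified from the data that the protocol requires, and the Month 14 anti-HBs GMT could be overstated in both groups.

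The size is unknown. The factors of 1.05 to 1.19 rest wholly on assumed values of p and k, and a reader should not take them, or any larger figure, as an estimate. The direction rests on the assumption that a further dose raises the titer. The Day 90 primary (anti-CS) and secondary (anti-HBs) analyses and the sample size are unaffected. This is a cheap improvement to one descriptive endpoint, not a threat to the trial's main conclusions.

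**What to change.** 1. **Recording (Section 6.9, Table 8 last row, Table 3 footnote d).** Extend the recording of hepatitis B-containing vaccines, with date and trade name, from the end of the existing window through the Month 4 to 13 home visits and Visit 7.
2. **Analysis (Sections 4.8 and 10.9.2).** Exclude children so vaccinated after Visit 6 from the Month 14 ATP anti-HBs analysis only. Keep them in the anti-CS, safety and Total Vaccinated Cohort analyses.

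The cost is one extra CRF item at contacts where concomitant medication is already recorded (Section 5.11), one sentence on the cohort, and perhaps a few children lost from one tertiary ATP analysis. The change concerns recording and analysis only and restricts no child's access to vaccination.
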